**Purpose**

Progressive multifocal leucoencephalopathy (PML) is a rare infectious disease of the brain, provoked by the JC virus. It usually occurs in subjects with impaired immune system as during HIV infection. To date, there is no specific antiviral treatment susceptible to cure PML. But in the setting of HIV-related PML, it was shown that combination antiretroviral therapy allows a restoration of the immune system and then might stop the progression of PML.

The objective of this study is to appreciate the supplementary efficiency brought by an association of more powerful antiretroviral molecules including enfuvirtide (FUZEON®) on the evolution of PML in HIV-1-infected patients. This research program will involve 30 patients in several centres in France. All the patients who will participate will receive enfuvirtide during 6 months in association with a combination of two or more potent antiretroviral drugs. The total duration of follow-up for a patient will be of 1 year.

Another aim of this study is to assess on treatment the evolution of immunological and virological factors related to JCvirus the causative agent of PML.

*Study Type*: Interventional

*Study Phase:* Phase II

*Study Design:* Treatment, Non-Randomized, Single Group Assignment, Open Label, Multicentre, Efficacy Study.

*Official Title:* Early intensification of combination antiretroviral therapy including enfuvirtide in the treatment of progressive multifocal leucoencephalopathy during HIV-1 infection. The ANRS 125 trial.

**Further Study Details:**

*Primary Outcome Measure:*

- Estimation by the method of Kaplan-Meier of the rate of survival at M12

*Secondary Outcome Measures:*

- Rate of survival and functional score (Modified Rankin Outcome Scale) at M12
- Evolution of the JC viral load in the CSF and percentage of patients with JC virus clearance of the CSF at M3 and M6
- Evolution of the CD4 and CD8 T cells sub- populations and of the antivirus JC specific T cell responses

*Expected Total Enrollment:* 30

*Study Start Date:* April 2005

*Study Completion Date:* December 2007

**Detailed Description:**

The aim of this open-label multicentre study is to estimate the effect of an early therapy intensification based on potent antiretroviral combination including enfuvirtide on survival in patients with HIV-1-related PML.

To demonstrate an expected one-year survival rate of 70%, significantly higher than 45% (the average of the one-year survival rate observed in previous reports), the inclusion of 24 patients is necessary. At last, 30 patients will be recruited towards the risk estimated at 25% of invalid inclusion.

Patients will be included on the following inclusion criteria : HIV-1 documented by Western Blot, clinical and radiological (MRI) evidence of active PML with clinical evolution (or deterioration) for less than 90 days, documentation of PML diagnosis for less than 30 days at the inclusion, informed consent (patient or confidence surrogate if decision making incapacity). Exclusion criteria will be the following: age less than 18-year-old; concomitant opportunistic infection of the central nervous system; pregnancy - feeding; co-infection by the HIV-2; history of immunotherapy (interleukin 2, alpha-interferon) or of treatment by enfuvirtide; history of treatment by cidofovir; contra-indication to receive enfuvirtide.

An independent committee will meet regularly to estimate the validity of PML diagnosis in included patients.

All the patients receive enfuvirtide during the first 6 months in association with a combination of two or more antiretroviral drugs which will be pursued during the next 6 months till the end of the study (M12). Antiretroviral-naïve patients will receive lopinavir/ritonavir, efavirenz, and tenofovir/emtricitabine (under the shape of TRUVADA®). For pretreated patients, antiretroviral combination will be chosen in every case on the basis of the therapeutic history and of the viral genotypes of resistance. Such association will contain at least two antiretroviral molecules, issued from two different families among the three following ones (nucleoside inhibitors of the reverse transcriptase, non-nucleoside inhibitors of the reverse transcriptase, protease inhibitors).

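### Thirty recruits do not secure the 24 necessary patients at the plan's own 25% invalid rate: about 22.5 valid patients are expected (minor)

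*Protocol*

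**What the plan says.** All three figures stand in the sample-size paragraph of the protocol's Detailed Description. The aim is set out as "To demonstrate an expected one-year survival rate of 70%, significantly higher than 45" per cent, the lower figure being an average from earlier reports. For this, "the inclusion of 24 patients is necessary". The next sentence gives the recruitment target: "At last, 30 patients will be recruited towards the risk estimated at 25% of invalid inclusion".

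The same section explains how an inclusion may turn out to be invalid: "An independent committee will meet regularly to estimate the validity of PML diagnosis in included patients". Validity is therefore judged after inclusion, among the patients who have been included.

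The target of 30 is repeated in Purpose ("This research program will involve 30 patients in several centres in France"), in Further Study Details and in the Abstract for patients. No section gives a larger target or provides for replacing invalid inclusions. The protocol does not show how 24 became 30, and it does not state the significance level, the sidedness or the power behind the 24.

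**The concern.** A risk that an inclusion is invalid applies to everyone recruited. To keep a required number of valid patients, that number is divided by the proportion expected to be valid. Multiplying it by one plus the invalid proportion gives too small a target. Here 30 is what the multiplication gives, and at the stated 25% it leaves fewer valid patients than the plan calls necessary.

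What is at stake is the size of the primary comparison. One-year survival is the primary outcome, and this paragraph is the only justification for the number of patients. As written, a reader would believe that 30 recruits protect 24 valid patients against 25% invalid inclusions, and they do not.

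**Working it through.** **Inputs from the protocol (Detailed Description)**
- Necessary patients: 24
- Anticipated invalid proportion: 25%
- Recruitment target: 30
- Reference and expected one-year survival: 45% and 70%

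**Inputs assumed because the protocol does not give them**
- Each inclusion is invalid independently with probability 25%.
- The test is one-sided at 5% with 80% planned power, using the normal approximation for one proportion.

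**Step 1. Reproduce the 30.** 24 × (1 + 0.25) = 24 × 1.25 = 30, an exact match. That this formula was used is inferred from the match.

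**Step 2. Allowance on recruited patients.** 24 / (1 − 0.25) = 24 / 0.75 = 32.

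**Step 3. What 30 recruits deliver.**
- Expected valid patients at 25% invalid: 30 × 0.75 = 22.5, which is 1.5 below 24.
- Invalid rate at which 30 leaves exactly 24: 1 − 24/30 = 20%.

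**Step 4. Chance of reaching 24 valid patients.** With the valid count distributed as Binomial(recruits, 0.75):
- 30 recruits: P(at least 24) = 0.348
- 32 recruits: P(at least 24) = 0.594

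**Step 5. Reproduce the 24 under the assumed level.**

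n = [(z₀.₉₅ √(p₀(1−p₀)) + z₀.₈₀ √(p₁(1−p₁))) / (p₁ − p₀)]²

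With p₀ = 0.45 and p₁ = 0.70:

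n = [(1.645 × 0.4975 + 0.842 × 0.4583) / 0.25]² = 23.2, rounded up to 24.

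The assumption is compatible with the plan's 24 but is not shown to be the one used. The same formula at one-sided 10% and 90% power gives 24.0, so the 24 does not identify its own alpha and power.

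**Step 6. Power at the numbers concerned.**

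Power = Φ{[(p₁ − p₀)√n − 1.645 √(p₀(1−p₀))] / √(p₁(1−p₁))}

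| Valid patients | Power (one-sided 5%, assumed) |
|---|---|
| 24 | 0.812 |
| 23 | 0.797 |
| 22 | 0.780 |

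The expected 22.5 lies between the last two rows, so the loss against 24 is roughly 1.5 to 3 percentage points.

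**The case against.** The best defence of the 30 is to read the 25% as an over-recruitment margin on the 24, since 6/24 = 25%. The three figures then agree. The English is loose enough that this cannot be excluded, but it is the less natural reading. The text speaks of "the risk estimated at 25% of invalid inclusion", and the committee judges validity in patients already included, so the denominator is the included patients. If a margin was meant, the sentence still needs rewording, because it describes a risk.

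The second objection is that the gap hardly matters: two recruits, or 1.5 expected valid patients, with power staying near 80% under the assumed level. This stands, and it is why the point is minor.

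A reader might go further and infer that the trial is materially underpowered. The documents do not support that. They state no alpha, power or test, and the primary outcome is a Kaplan–Meier estimate at M12, so any power figure is a reconstruction. Comparing exact binomial power at two particular sample sizes would not help either. With so few patients, exact power rises and falls from one n to the next, so the contrast would mostly reflect discreteness, and nothing in the protocol says such a test would be used.

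A reader might also take it as established that the planners multiplied by 1.25. The match is exact, but the formula is not in the document. The shortfall does not depend on it.

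**Conclusion.** The point holds as a minor arithmetic inconsistency. With a 25% risk applied to the patients included, 30 recruits are expected to leave 22.5 valid patients against the 24 called necessary. The chance of at least 24 is about 35%, on the assumption of independent invalidity at that rate. The target consistent with 24 and 25% is 32; the rate consistent with 24 and 30 is 20%.

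The size, 1.5 expected valid patients and a few points of power at most, rests on the assumed one-sided 5% level and the normal approximation. The error does not change the design, the endpoint or how the result would be interpreted. It is not a matter that a statistical analysis plan could settle, because the protocol itself fixes all three numbers.

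**What to change.** Keep 30 and rewrite the one sentence in the sample-size paragraph, in one of two ways:

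- State that 30 recruits with 25% invalid inclusions are expected to give about 22 valid patients, and restate the power at that number under the alpha and test actually used.
- State that 30 covers an invalid rate of 20%, if that rate can be defended.

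In either case, note that protecting 24 valid patients at 25% would take 32 recruits. The power quoted should come from the planned analysis, not from the reconstruction above.

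The cost is one sentence and, with the first option, a slightly less favourable power statement. Neither option needs more patients. Moving to 32 would add two, and the target of 30 would then also have to change in Purpose, Further Study Details and the Abstract for patients.

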***Criteria***

*Inclusion Criteria:*

- Men and non pregnant women
- 18 years of age and older
- Have confirmed laboratory diagnosis of HIV infection
- Presenting with a clinical history of active PML evolving (or continuing to deteriorate) for less than 90 days
- Diagnosis of PML documented for less than 30 days at the inclusion by cerebral imaging (MRI) AND the absence of another demonstrated etiology AND the detection of JCV DNA in the CSF by qualitative PCR
- Signed written inform consent

*Exclusion Criteria:*

- Concomitant opportunistic infection of the central nervous system
- Pregnancy – feeding
- Co-infection with the HIV-2
- History of immunotherapy including interleukine 2 or alpha-interferon
- History of treatment including enfuvirtide or cidofovir
- Contra-indication to receive enfuvirtide.

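### The diagnosis committee judges patients already included and treated open label, with no stated limit to baseline data or masking to survival, so exclusions could depend on the primary endpoint

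*Protocol*

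**What the plan says.** All of the following is in the protocol.

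- **Review after inclusion.** Detailed Description: "An independent committee will meet regularly to estimate the validity of PML diagnosis in included patients". The text does not say what material the committee sees, whether it knows the patient's course, or when a verdict becomes final.
- **Allowance for invalid inclusions.** Detailed Description, on showing 70% one-year survival against a historical 45%: "the inclusion of 24 patients is necessary", and then "30 patients will be recruited towards the risk estimated at 25% of invalid inclusion". What happens to a patient judged invalid is not stated.
- **Design.** Purpose: "Treatment, Non-Randomized, Single Group Assignment, Open Label, Multicentre, Efficacy Study".
- **Primary outcome.** Further Study Details: "Estimation by the method of Kaplan-Meier of the rate of survival at M12".
- **Entry diagnosis.** The inclusion criteria require three things together at inclusion: recent documentation on cerebral MRI, no other cause shown, and JC virus DNA found in the CSF by PCR.

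**The concern.** The committee meets repeatedly on patients who are already in the trial and on known treatment. By the time of a meeting, a patient may have died or clearly improved. If the committee knows this, a rapid death could be re-read as another disease, and a quick recovery could be re-read as not PML. Either verdict would make membership of the analysed set depend on the primary endpoint.

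A randomised trial might see such exclusions partly balance between arms. Here there is one arm and a fixed reference of 45%, so any selection passes straight into the estimate. The numbers are small enough for single patients to matter. With 16 survivors, the exact one-sided p-value against 45% is 0.067 for 16/26, 0.044 for 16/25 and 0.027 for 16/24. Taking one death out of the denominator moves the result across a 5% threshold.

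**Working it through.** **Inputs from the protocol (Detailed Description).** Reference survival p0 = 0.45, expected survival p1 = 0.70, 24 patients needed, 30 recruited, estimated 25% invalid.

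**Assumptions not in the protocol.** One-sided 5% test, 80% power, and a binomial count of survivors at month 12 in place of the Kaplan-Meier estimate (the two agree if every patient is followed to death or month 12). The ratios at which deaths or survivors are excluded are also assumed.

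**1. The planned 24.** n = [(1.645·√(0.45·0.55) + 0.842·√(0.70·0.30)) / 0.25]² = [(0.818 + 0.386)/0.25]² = 23.2, so 24. The figure is reproduced under these assumptions.

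**2. The step to 30.** 24 × 1.25 = 30. This step has a purpose only if invalid patients do not count towards the 24, which is why removal from the analysis is implied. An analysed set of 24 out of 30 means 6 exclusions. That is 6/24 = 25% of the valid patients and 6/30 = 20% of those recruited. The illustration below uses 6.

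**3. The success rule.** With 24 patients and true survival of 45%, P(at least 15) = 0.065 and P(at least 16) = 0.027. The smallest count that meets a one-sided 5% level is 16, so the rule is at least 16 of 24.

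**4. Selective exclusion under no effect.** Draw survivors among 30 from a binomial with p = 0.45. Remove 6 patients one at a time, giving each death a weight r relative to a survivor, and apply the rule to the remaining 24. Exact enumeration gives:

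| Exclusion pattern | Mean estimated survival | False-positive rate |
|---|---|---|
| Survivors twice as likely to be excluded | 41% | 1.1% |
| Unrelated to outcome (r = 1) | 45% | 2.7% |
| Deaths 1.5 times as likely | 47% | 4.4% |
| Deaths twice as likely | 49% | 6.0% |
| Deaths three times as likely | 50% | 8.6% |

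**5. Extremes.** If all 6 exclusions are deaths, the expected 30 × 0.45 = 13.5 survivors stand over 24, which is 56%. The rule is then met whenever at least 16 of the 30 survive, so the false-positive rate is P(at least 16 of 30 at 45%) = 0.231. If all 6 are survivors, the estimate is (13.5 − 6)/24 = 31%.

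**6. Analysing everyone.** With all 30 patients and no exclusions, a rule of at least 19 of 30 has a type I error of 0.033 at 45%. Its power is 0.841 if 70% survival holds in all included patients.

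**The case against.** The strongest reply is that this is a silence. The protocol does not say that the committee sees outcomes. What it sees, when it decides and which set is primary are often written in a charter or in a SAP, and neither is at hand. The committee is also described as independent, and entry already requires MRI and a positive CSF PCR, so it is hard to re-read an early death as another disease.

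Much of this stands, and it limits the point:

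- A reader might infer that up to a quarter of patients may be dropped. The 25% is a planning estimate of risk, not a cap.
- A reader might infer that the protocol removes invalid patients from the primary analysis. It does not say so, and it does not say that the committee's verdict defines an invalid inclusion. Both are implied by the sample-size step.
- A reader might infer that the survival estimate will be biased upwards. Nothing in the document shows bias, and selection could equally run downwards.
- No passage supports deaths being two or three times as likely to be excluded. At 1.5 times, the false-positive rate stays below 5%.

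What does not stand is that the gap can safely wait. Independence is not masking. The entry criterion that no other cause has been shown remains a judgement, and later events could colour it. The plan's own allowance of 25% shows that entry criteria alone are not expected to settle validity. A SAP can add a sensitivity analysis, but it cannot undo verdicts already reached with the outcome known.

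**Conclusion.** The point holds as a cheap improvement of low to moderate severity. The protocol sets up diagnostic review after inclusion in an open-label single-arm trial and allows for a sizeable invalid fraction. It neither restricts the committee to baseline data nor masks it to survival. Outcome-dependent exclusion is possible, not demonstrated, and its direction is open.

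Under the stated assumptions, moderate selection against deaths (two to three times) moves the false-positive rate from 2.7% to about 6% to 9%, and the mean estimate from 45% to about 49% to 50%. That is a shift of 4 to 5 points against a planned difference of 25. The 23% figure is an extreme bound. Selection against survivors makes the test conservative, at about 1%. All of these figures depend on the assumed test, success rule, exclusion ratios and number excluded, and on the implied reading that invalid patients leave the primary analysis.

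**What to change.** State in the protocol, or in a charter that it refers to:

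1. The committee decides once per patient, soon after inclusion. It uses only the baseline dossier: history, MRI, CSF PCR and the work-up for other causes up to inclusion. It is masked to treatment course and vital status.
2. Whether patients judged invalid leave the primary analysis.
3. Kaplan-Meier survival at month 12 is reported in all included and treated patients beside the estimate in those with a valid diagnosis.

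There is no need to make a claim conditional on the two estimates agreeing. Such a rule would be a preference, and the reader can judge from both figures.

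The cost is some wording on committee procedure and one extra survival estimate. The committee is already planned, and the entry criteria already call for most of the dossier. The small downside is that an alternative diagnosis emerging later no longer removes a patient from the valid-diagnosis set and is handled in a sensitivity analysis instead.

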**Eligibility**

*Ages Eligible for Study:* 18 Years and older

*Genders Eligible for Study:* Both

*Accepts Healthy Volunteers:* No

***Criteria***

*Inclusion Criteria:*

- Men and non pregnant women
- 18 years of age and older
- Have confirmed laboratory diagnosis of HIV infection
- Presenting with a clinical history of active PML evolving (or continuing to deteriorate) for less than 90 days
- Diagnosis of PML documented for less than 30 days at the inclusion by cerebral imaging (MRI) AND the absence of another demonstrated etiology AND the detection of JCV DNA in the CSF by qualitative PCR
- Signed written inform consent

*Exclusion Criteria:*

- Concomitant opportunistic infection of the central nervous system
- Pregnancy – feeding
- Co-infection with the HIV-2
- History of immunotherapy including interleukine 2 or alpha-interferon
- History of treatment including enfuvirtide or cidofovir
- Contra-indication to receive enfuvirtide.

**Abstract for patients**

Progressive multifocal leucoencephalopathy (PML) is a rare infectious disease of the brain, provoked by the JC virus. It usually occurs in subjects with impaired immune system as during HIV infection.To date, there is no specific antiviral treatment susceptible to cure PML. But it was shown in the setting of HIV-related PML, that combination antiretroviral therapy allows a restoration of the immune system and then might stop the progression of PML.

The objective of this study is to appreciate the supplementary efficiency brought by an association of more powerful antiretroviral molecules including FUZEON® on the evolution of PML. This research program will involve 30 patients in several centres in France. All the patients who will participate will receive FUZEON® during 6 months in association with a combination of two or more potent antiretroviral drugs. The total duration of follow-up for a patient will be of 1 year.
